**Fig. 2 Fig2:**
[figure not shown]
Stepped wedge cluster randomized trial to assess implementation outcomes

**Fig. 3 Fig3:**
[figure not shown]
Modified CONSORT diagram describing stratified block randomization. *We will use stratified randomized, stratified by tertiles of each site’s number of HUD-VASH full-time equivalent (FTE) employees (proxy for size and resources). REP = Replicating Effective Programs; CE = Consumer Engagement

### Evaluation

We will evaluate our EBPs’ implementation and effectiveness, with the goals of: 1) capturing fidelity to REP and CE; 2) comparing MAT and CBT-SUD reach, adoption and sustainment achieved by REP and REP + CE, and between REP vs. REP + CE; 3) comparing Veteran outcomes (housing stability, acute care use) and Veteran and provider experiences achieved by the strategies and EBPs; and 4) comparing costs and budget impact for EBPs and strategies. Below, we describe the methods for each goal, followed by methods for qualitative data collection and analyses that cut across goals. Of note, if we receive a request for access to our evaluation data, we will establish a Data Use Agreement (DUA). The DUA will enable a limited dataset, excluding all identifiers, and prohibiting the recipient from identifying or re-identifying any individual whose data are included.

#### Fidelity to REP and CE

Fidelity to REP and CE will be assessed in three domains [37]: adherence (extent to which strategies took place); dose (amount of each strategy received and proportion of providers and HEVs who received each strategy); and responsiveness (receptivity and involvement of providers and HEVs to strategies).

We will maintain an Implementation Activity Log that summarizes all project activities pertaining to REP and CE. The log will include dates and times of all training and TA (across both EBPs); attendees; and open-ended, templated notes on the implementation process. All CE encounters by HUD-VASH peers will be recorded in a templated Electronic Health Record (EHR) note with checkboxes for activities performed [38] and space for free text about CE content. We will abstract data from these notes to augment the Implementation Activity Log. Adherence to implementation strategies will be assessed by comparing this log and abstracted data to processes described in the implementation strategies above. To assess adherence to REP specific to MAT, we will use an existing “advanced skill training fidelity tool” to assess adherence to core components of AD. For CBT-SUD, consultants will record TA activities in the Implementation Activity Log.

Dose will be captured by describing the frequency of training/TA and CE delivered to each site (and % of eligible participants attending). Responsiveness will be characterized by analyzing data from open-ended log notes (including free text in peer notes) and periodic reflections (brief, ethnographically informed, guided discussions) [39] with HUD-VASH supervisors that capture implementation context; and interviews with HUD-VASH staff at 18 months post-implementation.

#### MAT and CBT-SUD reach, adoption, and sustainment

Table 3 lists measures for reach, adoption, and sustainment. Measures of reach for MAT indicate one prescription (30–90 days/duration) and use of MAT for 180 days [40]. For CBT-SUD, reach assesses a single visit and a threshold of 9 visits (which may equate to meaningful impacts in substance use/functioning) [41]. We will use VA administrative data to abstract these measures for HEVs in HUD-VASH at implementation sites. Sustainment will reflect these reach and adoption measures after our intensive implementation supports end (cross-sectionally at 9 months after we end each implementation cohort).

**Table 3 Tab3:** Reach, adoption, and sustainment measures

	**MAT**	**CBT-SUD**
Reach^*^	• % HEVs who used MOUD for OUD, ≥ 1 prescription • % HEVs who used MOUD for OUD for 180 days since initial prescription (without a break ≥ 14 days in supply) • % HEVs who used MAUD for AUD, ≥ 1 prescription • % HEVs who used MAUD for AUD for 180 days since initial prescription (without a break ≥ 14 days in supply)	• % HEVs with SUD with ≥ 1 CBT-SUD visit • % HEVs with SUD with ≥ 9 CBT-SUD visits
Adoption^*^	• % HUD-VASH and mental health prescribers engaged with HEVs^**^ who ordered MOUD/MAUD at least once in the Electronic Health Record	• % HUD-VASH case managers who delivered ≥ 1 CBT-SUD session
Sustainment^¶^	• Reach and adoption measures described above	Reach and adoption measures described above

^*^Reach and adoption measures will be assessed at 18 months post-implementation

^**^Mental health prescribers engaged with HEVs will be defined as prescribers listed on AD dashboards, i.e., most recent mental health prescriber for Veterans who had ≥ 2 billable HUD-VASH encounters in the past year (§B3bi)

^¶^Sustainment will be assessed 9 months after we conclude REP vs. REP + CE for each cohort. HEVs referenced in this table include HEVs enrolled in HUD-VASH at implementation sites

We will use a staggered adoption model [42], comparing reach and adoption pre-CARE-VASH, to REP alone, and to REP + CE. These models utilize fixed effects for sites to account for time-invariant confounders between sites as well as fixed effects for time-period to account for secular trends. We will implement this approach [42] using a doubly robust estimator based on stabilized inverse probability weighting [43], with weights based on HEV demographics and comorbidities (using the Multimorbidity-Weighted Index) [44]. The average treatment effect on the treated will be estimated based on comparison to the not-yet-treated periods and presented using an event-study approach which will estimate the intervention effect across time (i.e., for each quarter-year). In addition to providing intervention estimates for each quarter-year of the study, a pooled intervention effect estimate will be aggregated across the study period by taking weighted averages of the event-study estimates with non-parametric bootstrapping (1000 replications) used to provide standard errors for aggregated estimates. Sustainment will be compared between sites that received REP vs. REP + CE, with reach and adoption measures adjusted as described.

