**Methods:**

We will use Replicating Effective Programs (REP) to implement MAT and CBT-SUD at 12 sites over 18 months. After 9 months of REP alone, half (n = 6) of these sites will also receive Consumer Engagement (CE) for 9 months, activating HEVs to adopt these practices via peer coaching. We will conduct a type 3 hybrid cluster-randomized trial to compare the impacts of REP versus REP + CE. Randomization will occur at two levels: implementation start date (3 cohorts) and the implementation strategy (REP versus REP + CE). We will use stratified block randomization to balance site size among sites receiving each strategy across cohorts. We will use mixed methods to assess the impacts of REP versus REP + CE on implementation outcomes (reach [primary outcome], adoption, and sustainment); Veteran outcomes (primarily housing); provider and Veteran experiences; and costs and budget impacts. We hypothesize that REP + CE will have higher implementation costs than REP but result in improved MAT and CBT-SUD implementation and Veteran outcomes, leading to a business case for REP + CE.

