### Study design

We plan a type 3 hybrid implementation-effectiveness trial [14], registered as NCT07141394 on 8/26/2025 and determined to be non-research by VA’s Central Institutional Review Board. We will use stratified block randomization, stratified by tertiles of each site’s number of HUD-VASH full-time equivalent (FTE) employees (proxy for size and resources).

Within the 12 sites, we will use a stepped wedge cluster randomized trial design [35] (Fig. 2) to study implementation outcomes, balanced for allocation to treatment timing and assignment to REP vs. REP + CE arms across 3 strata of 4 sites each (Fig. 3). Using a random number generator with assignment by our statistician, each stratum will be randomly assigned to 1 of 3 possible cohort pairings (cohorts 1 & 2; 2 & 3; 1 & 3). Within each stratum, 4 sites will be randomly assigned to 1 of the 2 cohorts in the pair, ensuring that there are early and late treatment timings within each stratum. Within each stratum-cohort combination (n = 2), the REP vs. REP + CE implementation strategy arm will be randomly assigned, and consent obtained thereafter. The staggering of sites into cohorts is necessary to provide HUD-VASH sites with optimal EBP and CE training within our resources. We selected the 9-month duration of REP, before augmenting with 9 months of CE at REP + CE sites, because we found this duration of REP to be effective in prior trials of a psychosocial EBP for HEVs [36]. We will be unable to blind sites (clusters) assigned to CE augmentation, as we need to engage with leadership regarding peer supports’ commitments. To optimize power in our effectiveness analyses, we will compare sites that receive REP vs. REP + CE vs. all other HUD-VASH sites in the nation that are not engaged in CARE-VASH.

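### The 180-day MOUD and MAUD reach measures are read at month 18, when CE ends, so starts in about 5.9 of the 9 CE months cannot qualify

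*Protocol article*

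**What the plan says.** The abstract names reach as the primary outcome and sets the calendar: "We will use Replicating Effective Programs (REP) to implement MAT and CBT-SUD at 12 sites over 18 months". Six of the sites also receive CE. The Study design section places it in the second half: "We selected the 9-month duration of REP, before augmenting with 9 months of CE at REP + CE sites".

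The section on reach, adoption and sustainment gives two kinds of MAT measure: "Measures of reach for MAT indicate one prescription (30–90 days/duration) and use of MAT for 180 days". In Table 3 the longer measure for opioid use disorder is the percentage of "HEVs who used MOUD for OUD for 180 days since initial prescription (without a break ≥ 14 days in supply"). The alcohol measure has the same form: "HEVs who used MAUD for AUD for 180 days since initial prescription (without a break ≥ 14 days in supply").

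The footnotes give the reading times. For reach: "Reach and adoption measures will be assessed at 18 months post-implementation". For the later reading of the same measures: "Sustainment will be assessed 9 months after we conclude REP vs. REP + CE for each cohort".

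The analysis is a staggered adoption model presented as an event study, which will "estimate the intervention effect across time (i.e., for each quarter-year"), with the quarterly estimates then pooled.

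**The concern.** A measure that takes 180 days to complete is read on the day the added strategy ends, and that strategy has by then run for only nine months. A Veteran whom a peer coach prompts to start MAT in month 14, and who then stays on it without a break, has had about four months to accumulate use by the reading. On the footnote as written, this person does not meet the measure, whatever happens later.

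This matters because REP versus REP + CE is the trial's central contrast. The section on REP + CE says that peers will work with Veterans who are not engaged in SUD care, so new or renewed starts are a main route by which CE could act. On the two 180-day measures, most of the CE calendar cannot register that route. A weak or null CE result on sustained use could then reflect the reading date and not the strategy.

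**Working it through.** The plan states no figure for this point, so there is none to reproduce. The check is calendar arithmetic.

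**Inputs**
- CE period: months 9 to 18 (Abstract, Methods; Study design).
- Reading of reach: month 18 (Table 3 footnote). This has to be counted from the start of implementation. Counted from the end of the strategies it would be month 18 + 18 = 36, later than sustainment at month 18 + 9 = 27.
- Required duration: 180 days from first prescription (Table 3).
- Month length: 30.4375 days (convention).
- Timing of MAT starts within the CE period: not given, so assumed and varied below.

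**Latest start that can qualify**
- 180 / 30.4375 = 5.91 months.
- 18 − 5.91 = month 12.09.

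**Part of the CE period that can and cannot yield a success**
- Can: 12.09 − 9 = 3.09 months; 3.09 / 9 = 34%.
- Cannot: 5.91 months; 5.91 / 9 = 66%. With 30-day months it is 6 / 9 = 67%.
- If a final supply gap of up to 13 days is tolerated, 167 days suffice: 167 / (9 × 30.4375) = 61%.

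**Share of CE-era starters affected**, with u = 0.657 the excluded fraction of the period and c = 1 − u = 0.343:

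| Pattern of starts over months 9 to 18 | Formula | Cannot qualify |
|---|---|---|
| Even | u | 66% |
| Linearly front-loaded | u² | 43% |
| Linearly back-loaded | 1 − c² | 88% |
| Even, but only from month 10 | 180 / (8 × 30.4375) | 74% |
| Even, but only from month 11 | 180 / (7 × 30.4375) | 84% |

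**Effect on the contrast.** Suppose persistence does not depend on when a person starts. The part of a CE effect that comes through new starts then appears at 1 − (share excluded) of its full size: 34% with even starts, 57% front-loaded, 12% back-loaded. These percentages apply to that part only.

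**Route that remains visible.** A Veteran who starts between month 9 − 5.91 = 3.09 and month 9 has a 180-day window that overlaps the CE period and closes by month 9 + 5.91 = 14.91, before the reading. A CE effect on that person's persistence can be seen.

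**With full follow-up.** The last CE-era starter completes 180 days at month 18 + 5.91 = 23.91, and the share excluded by time falls to 0%. The planned month-27 reading leaves 9 × 30.4375 = 274 days after CE ends. This exceeds 180, so no CE-era starter is excluded by time there.

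**The case against.** The strongest reply is that the article does not call month 18 a data cut-off. The measure is already defined from the first prescription, and follow-up windows and the assignment of a person to a quarter are details that an article leaves to the full protocol or SAP. In part this stands: the footnote does not rule out later follow-up. But the point does not rest on silence. The article states the duration, the reading time and the CE calendar, and taken together as written they exclude most of the CE period.

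A second reply is that the damage is contained, and it is. Only two of the six reach measures in Table 3 are involved. Late starters still count on the measures of at least one prescription. The power section works from rates of current receipt, not of 180-day use. The sustainment comparison at month 27 has enough time for every CE-era starter. That reading is a cross-sectional one after supports end, however, so it does not repair the month-18 reach result.

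A reader might infer more than the documents support:
- *That any CE effect on 180-day use shrinks to one third.* This needs even starts and an effect through new starts alone. Table 2 also gives CE the aim of improving adherence, and for earlier starters that effect would partly show.
- *That the cut-off creates a false difference between arms.* Both arms have the same cut-off.
- *That the comparison with the period before CARE-VASH is biased.* Nothing in the article gives that period fuller follow-up.
- *That a 180-day outcome cannot enter a quarterly event study.* It can, if it is attributed to the quarter of initiation.
- *That the threshold of nine CBT-SUD visits has the same defect.* It needs a much shorter time, and no size has been worked out for it.

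**Conclusion.** The point holds for the two 180-day MAT reach measures. On the plain reading of the Table 3 footnote, starts after about month 12.1 cannot qualify, so 5.9 of the 9 CE months cannot yield a success. In persons, this is 66% of CE-era starters if starts are even and about 43% to 88% under linear front- or back-loading. The consequence is dilution of the REP + CE versus REP difference, limited to new starts on these measures.

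The conclusion rests on two assumptions: that month 18 is where ascertainment stops, and a pattern of starts that the article does not give. The first decides whether the problem exists; the second changes only its size. It should be corrected, because reach is the primary outcome and CE is the randomized addition, but it does not undermine the other reach measures.

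**What to change.** Keep the Table 3 definitions and denominators and change only the follow-up. For every person whose first MOUD or MAUD prescription falls in the pre-CARE-VASH, REP or REP + CE period:
- ascertain supply for 180 days after that person's own first prescription, which for the last CE-era starters runs to about month 24;
- attribute the result to the quarter of initiation in the event study;
- apply the same rule in every period and both arms.

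Amend the footnote so that month 18 closes initiation for these two measures and not ascertainment. If the full protocol already does this, the article needs only a sentence saying so.

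The measures come from VA administrative data, and a reading at month 27 is already planned, so the change is mainly wording and code. There are two costs. The result for these measures arrives about six months later (month 23.9 against month 18). Part of the follow-up for late starters also falls after implementation support has ended. The plan should say so and distinguish this follow-up from sustainment, which is a separate cross-sectional reading at month 27.

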## Methods

### Overview

We will conduct a cluster-randomized trial comparing sites (or clusters) randomized to REP versus REP + CE. Specifically, we will conduct a type 3 hybrid implementation-effectiveness trial [14] using a stepped wedge design with randomization at two levels: implementation start date (3 cohorts) and implementation strategy (REP vs. REP + CE). We will use stratified block randomization to balance site size among sites receiving each strategy across cohorts. We will use mixed methods to assess the impacts of REP vs. REP + CE. We hypothesize that REP + CE will have higher implementation costs than REP, but result in improved and more equitable EBP reach, adoption, sustainment, and housing outcomes, leading to a business case for REP + CE.

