#### Sample size and power

Across the 12 sites, we will have 7908 HEVs undergoing REP or REP + CE. For assessing reach, we will examine the proportion of eligible HEVs who receive MAT and the proportion of eligible HEVs who receive CBT-SUD. Among HUD-VASH Veterans with AUD (53%) and OUD (16%), ~ 9.9% and 19.9% currently receive MAT, respectively. Over half (66%) are eligible for CBT-SUD, though only 0.5% receive it. We can approximate the power of our staggered adoption model approach to compare REP alone (or REP + CE) to pre-CARE-VASH based on the power to detect a difference in proportion assuming a within-site correlation of outcomes over time of rho = 0.04. With this sample size using a two-sided alpha level of 0.05, we would have 80% power to minimally detect an absolute increase in reach for MAUD of 2.7 percentage points, MOUD of 6.6 percentage points, and CBT-SUD of 0.8 percentage points. These minimally detectable estimates are much smaller than those found for a MAUD implementation effort [45] and an MOUD implementation study [46]. Though a systematic review of CBT implementation studies note that the implementation evaluations did not address changes in reach [47], we can extrapolate from MAT studies to estimate that concerted implementation efforts would achieve an increase in CBT-SUD’s reach of > 0.8 percentage points.

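### The randomised REP + CE versus REP contrast on reach, the primary outcome, has no stated estimand, control set or detectable difference; the plan fixes these only against not-yet-treated (pre-CARE-VASH) periods

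*Protocol article*

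**What the plan says.** The Abstract (Methods) sets the question: "We will conduct a type 3 hybrid cluster-randomized trial to compare the impacts of REP versus REP + CE", and names reach as the primary outcome. The Evaluation section repeats it as a goal: "comparing MAT and CBT-SUD reach, adoption and sustainment achieved by REP and REP + CE, and between REP vs. REP + CE". Study design supplies the matching randomisation: "Within each stratum-cohort combination (n = 2), the REP vs. REP + CE implementation strategy arm will be randomly assigned". With three strata and two cohorts per stratum, that gives six pairs of sites, one site per arm, starting together. On timing, the Abstract says: "After 9 months of REP alone, half (n = 6) of these sites will also receive Consumer Engagement (CE) for 9 months".

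For analysis, the section on MAT and CBT-SUD reach, adoption and sustainment announces a staggered adoption model "comparing reach and adoption pre-CARE-VASH, to REP alone, and to REP + CE". It then fixes the effect and its comparator: "The average treatment effect on the treated will be estimated based on comparison to the not-yet-treated periods". Quarterly event-study estimates are averaged into one pooled effect.

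Sample size and power describes the purpose of the same model as being to "compare REP alone (or REP + CE) to pre-CARE-VASH", and its detectable differences (MAUD 2.7, MOUD 6.6, CBT-SUD 0.8 points) refer to that comparison.

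Elsewhere the arms are compared directly: sustainment in the same section, ED visits and hospitalisations under Acute care use, and utilisation costs under Budget impact analysis.

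**The concern.** The comparator written down for the primary outcome is not the one the arm randomisation provides. All 12 sites start REP, so once the third cohort starts no site remains in its pre-CARE-VASH period. CE begins nine months after each site's start, so CE exposure falls where such controls are scarce or gone. Meanwhile every REP + CE site has a REP-only partner of the same size stratum and start date, and the text never names these partners as controls for reach.

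Read literally, the head-to-head answer on reach would have to be pieced together from two effects, each measured against periods before the programme, without using the paired allocation. The power section would also reassure readers about a comparison other than the trial's main hypothesis.

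**Working it through.** **1. Reproducing the stated detectable differences.** Inputs from Sample size and power: 7908 HEVs; AUD 53%, OUD 16%, CBT-SUD-eligible 66%; baseline reach 9.9%, 19.9%, 0.5%; two-sided alpha 0.05; power 80%; rho = 0.04 within site over time. Eligible HEVs: 7908 × 0.53 = 4191; × 0.16 = 1265; × 0.66 = 5219. Half of each (six sites' worth): 2096, 633, 2610.

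Formula: n per group = [1.960·√(2p̄(1−p̄)) + 0.842·√(p₁(1−p₁) + p₂(1−p₂))]² / d², solved for d = p₂ − p₁.

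With no inflation for clustering, d = 2.74 (MAUD), 6.65 (MOUD) and 0.71 (CBT-SUD) points, against 2.7, 6.6 and 0.8 stated. CBT-SUD rounds to 0.8 only with a continuity correction (0.76), so no single variant tried returns all three. The match is close enough to show that the figures correspond to groups of six sites' size with essentially no between-site variance. That may be defensible for a before-after comparison within sites. It cannot be assumed for a comparison between two sets of six sites.

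**2. The same formula for 6 versus 6 sites.** The documents give no between-site ICC, so it is an assumption here. Average eligible HEVs per site, m: 349.3, 105.4, 434.9. Design effect = 1 + (m − 1)·ICC; group sizes are divided by it. Example, MAUD at 0.01: 1 + 348.3 × 0.01 = 4.48; 2096 / 4.48 = 468; d = 6.2 points.

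| Assumed ICC | Design effects (MAUD / MOUD / CBT-SUD) | Detectable difference, points |
|---|---|---|
| 0.001 | 1.35 / 1.10 / 1.43 | 3.2 / 7.0 / 0.9 |
| 0.01 | 4.48 / 2.04 / 5.34 | 6.2 / 9.7 / 2.3 |
| 0.04 | 14.9 / 5.2 / 18.4 | 12.2 / 16.0 / 6.1 |

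At 0.04, a t test on 10 degrees of freedom gives 13.6 / 17.7 / 7.2. All of these use post-period data only; baseline adjustment or site fixed effects would lower them.

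**3. Concurrent pre-CARE-VASH controls during CE.** There are 6 sites × 9 months = 54 CE site-months. Two REP + CE sites per cohort follows from the staff interview plan: 6 peers per cohort at 3 per REP + CE site. The gap between cohort starts is not in the text, so equal spacing of s months is assumed. Cohort 3 starts at month 2s, and after that no site is not yet started. Covered CE months per site:

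- cohort 1: min(9, max(0, 2s − 9))
- cohort 2: min(9, max(0, s − 9))
- cohort 3: 0

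| s (months) | Covered site-months | Uncovered |
|---|---|---|
| 3 | 0 | 54 of 54 |
| 6 | 2 × (3 + 0) = 6 | 48 of 54 |
| 9 | 2 × (9 + 0) = 18 | 36 of 54 |
| 12 | 2 × (9 + 3) = 24 | 30 of 54 |
| 13.5 | 2 × (9 + 4.5) = 27 | 27 of 54 |
| 18 | 2 × (9 + 9) = 36 | 18 of 54 |

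Cohort 3's 2 × 9 = 18 site-months are uncovered whatever s is. At the 18-month assessment in Table 3, cohort 1 has a not-yet-started site only if 2s > 18, cohort 2 only if s > 18, and cohort 3 never. Against the paired REP-only site, all 54 site-months have a concurrent randomised control.

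**The case against.** The strongest reply is that the contrast is planned. The Evaluation section names it, the reach model lists all three conditions, sustainment (the same measures, nine months later) is compared between arms, and the budget impact analysis applies the same staggered-adoption estimator to REP versus REP + CE costs. Not-yet-treated is also not defined as pre-CARE-VASH only. It could include REP periods before CE, and the Discussion says the phased start is meant to allow within-site analyses.

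Much of this stands, and it limits the point. A reader might infer that the head-to-head contrast will not be estimated at all; the documents do not support that. What is missing is a reach estimand and control set for it. The wider reading of not-yet-treated is possible, but the power section describes the model as a comparison with pre-CARE-VASH, which favours the narrower one.

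A reader might also infer that most CE site-months lack a control. That holds only for a gap under 13.5 months and only against pre-CARE-VASH sites. The design itself does contain valid controls.

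Nor do the documents show that secular change would be confounded with CE. Start dates are randomised, period effects are in the model, and cells without controls would normally go unestimated. The likely loss is coverage and efficiency, not demonstrated bias.

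Finally, the funder fixed 12 sites, so a head-to-head detectable difference would guide interpretation rather than sample size. That is true, but the reader still needs it to interpret a null result.

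**Conclusion.** The point holds in this form: the primary outcome's stated comparator and its only power statement concern each strategy against not-yet-treated, pre-CARE-VASH periods, while the randomised question is REP + CE against REP. This is more than condensed detail, because the article commits to a comparator and the direct contrast is spelled out for other outcomes.

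Under the narrower reading, 18 of 54 CE site-months are certainly without a concurrent control, given two REP + CE sites per cohort. Anything beyond that depends on the assumed spacing of cohorts. The published 2.7, 6.6 and 0.8 points cannot stand in for the head-to-head precision. The replacement figures rest on an assumed ICC and an unadjusted post-period comparison, so they show the scale of the change and are not the trial's actual power.

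**What to change.** - State REP + CE minus REP as the main reach estimand, either over the CE period or at the 18-month assessment, as change from the pre-CE period. Choose the window by measure: an HEV who starts medication late in the CE period cannot complete 180 days of use within it.
- Define CE as the treatment in the estimator, with the REP-only site of the same stratum-cohort pair as control.
- Use small-sample inference for 6 versus 6 sites. A permutation of arm within pairs is one option: 2⁶ = 64 allocations, smallest two-sided p = 2/64 = 0.031.
- Keep each strategy versus pre-CARE-VASH as secondary, limited to quarters that still have a not-yet-started site. Using national non-CARE-VASH sites as further controls is optional; it would extend the plan, which reserves them for the effectiveness analyses.
- Say that the existing detectable differences apply only to the pre-CARE-VASH comparison. Add the head-to-head figure under a stated between-site ICC, with and without baseline adjustment.

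This needs revised analysis wording and code. No new sites or data are required unless the optional national controls are added. The downside is that the stated precision for the main question becomes less favourable.
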